#### Evolution of lung disease

The evolution of leptospirotic pneumonitis is evaluated by way of lung auscultation, radiological evaluation, gasometric evaluation and hematometry (hematocrit and hemoglobin) on a daily basis up to the seventh day and then on the 14th and 28th days. Respiratory auscultation is used to determine the presence of crackles. Once these have been identified, their severity is classified according to the extent of lung involvement (Table 2).

**Table 2 T2:** Extent of lung involvement on respiratory auscultation

Severity of lung involvement	Extent of lung involvement on respiratory auscultation
Slight	Lower third
Moderate	Lower two thirds
Severe	Whole lung

A lung auscultation is carried out again on the fifth day of the patient's follow-up and categorized according to whether it is improving or worsening. It is considered to be improving when there is a reduction in the parameters described above and considered to be worsening if there is no change or if there has been an increase in the parameters.

The radiological evaluation aims to determine the presence and the extent of pulmonary infiltrate. When present, it is categorized according to its extent and severity (Table 3).

**Table 3 T3:** Extent of lung involvement according to radiological examination

Severity of lung involvment	Extent of lung involvement according to radiological examination
Slight	Lower third
Moderate	Lower two thirds
Severe	Whole lung

Another radiological examination is carried out on the fifth day of the patient's follow-up and categorized as improving or worsening. It is considered to be improving when there is a decline in the radiological parameters described above. It is considered to have worsened when the parameters have remained unchanged or seen an increase.

In the gasometric evaluation the relation between PaO2/FiO2 is used in order to establish whether there has been an improvement or a decline. It is measured again on the fifth day and categorized as having improved when the value is equal to or greater than 300 and as having declined when the value is less than 300.

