The evolution of hematometry is measured by way of hematocrit and hemoglobin levels and considered when there is a decrease of over three percentage points in hematocrit and 1 g/dl in hemoglobin, with no evidence of blood loss. The intensity of bleeding from the lungs is categorized as slight, when the hematocrit loss is more than three and less than five percentage points, moderate when greater than five but less than ten percentage points, and severe when it is greater than ten percentage points. The evolution of hematometry is evaluated on the fifth day of the patient's follow-up and is categorized as having improved when there has been no drop in hematometry or when it is kept in levels considered acceptable, when blood transfusion is necessary. It is considered to have declined when the hematometry remains unchanged after hemotransfusion or when there is an increased drop in hematometry.

Patients are considered to have improved, irrespective of the extent of the improvement, when, after five days of follow-up, there has been an improvement in three of the four parameters evaluated: lung auscultation, radiological evaluation of pulmonary infiltrate, arterial gasometry and hematometry. Improvement is considered to be early when it occurs within the first forty-eight hours and late when it occurs later than this. Treatment is considered to have failed when the patient does not show improvement in three of the four parameters listed above.

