### Sample size

The sample size was calculated on the basis of a statistical significance (alpha error) of 5%, a power of 80%, corresponding to a beta error of 20%. The expected mortality for leptospirotic pneumonitis is 30%. For a reduction of 50% in mortality, the expected mortality in patients treated with corticosteroids would be 15%. The sample size calculated was 133 patients for each group. The same parameters were used to obtain statistical significance and a standard deviation of 21 days for duration of mechanical ventilation, giving an expected sample of 33 patients per group. For the duration of ICU stay variable, the same parameters were used to obtain statistical significance and a standard deviation of 8 days, giving an expected sample of 23 patients per group.

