### Statistical analysis

Double data enter is performed using EPI INFO Version 6.0, giving rise to two datasets that can be compared to detect possible typing errors. The dataset is subsequently checked for consistency. The distribution of potential confounding factors in the two treatment groups are compared to check randomization.

The main analysis will be carried out through comparison of the various outcomes in the two groups, by calculating the percentage distribution and the relative risk. The 95-% confidence interval and the chi-squared test will be used to test statistical association. The t-test will be used to compare the means. The results are considered statistically significant when the p-value is less than 0.05. The efficacy of the intervention is calculated according to the following formula:

Patients randomly included in the study who, for whatever reason, including transfer to another hospital, do not receive the treatment for which they were assigned are considered to belong to the group to which they were allocated **(intention to treat analysis)**. These will be deemed treatment failure. The patients who do not receive confirmation from the laboratory of diagnosis of leptospirosis will still be included in the analysis. They will not be considered as losses or treatment failure. Data analysis will be carried out using EPI INFO Version 6.0 and SPSS 8.0.

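### Lung evolution, the first-listed secondary outcome, is reduced to a day-5 improved-or-failed score with PaO2/FiO2 cut at 300 whatever its entry value, which discards graded data the trial already collects

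*Protocol article*

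**What the plan says.** Under *Evolution of lung disease*, the protocol article collects auscultation, chest film, blood gases and hematometry daily to day 7 and again on days 14 and 28. Auscultation and film extent are graded on three levels (Tables 2 and 3). PaO2/FiO2, hematocrit and hemoglobin are continuous.

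The same section then reduces these data twice.

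- **Each parameter becomes a two-way day-5 score.** For PaO2/FiO2 the value is "categorized as having improved when the value is equal to or greater than 300 and as having declined when the value is less than 300". Auscultation and film count as improved only if the extent has fallen; an unchanged grade counts as worsening.
- **The four scores become one.** "Patients are considered to have improved, irrespective of the extent of the improvement" if three of the four parameters improve, and "Treatment is considered to have failed when the patient does not show improvement in three of the four parameters listed above". Patients who improve also receive an early (first 48 hours) or late label.

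*Statistical analysis* compares the various outcomes "by calculating the percentage distribution and the relative risk. The 95-% confidence interval and the chi-squared test will be used to test statistical association", and means by t-test. It does not name the test for lung evolution. *Study design* and Table 1 list lung evolution first among the secondary outcomes. *Sample size* gives planning figures for mortality, ventilation time and ICU stay, but none for lung evolution.

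**The concern.** Two things are wrong with the score.

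**It ignores distance.** A day-5 ratio of 305 counts the same as 450, and 295 the same as 80. Two improved parameters count the same as none. The early/late label does not repair this, because it only subdivides patients already called improved and says nothing about how much they improved.

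**The PaO2/FiO2 item does not measure change.** Under *Diagnosis of Leptospirotic pneumonitis*, hypoxemia is only one of several findings that can accompany the infiltrate, so a patient may enter with a ratio of 300 or more. If that ratio is the same on day 5, the item reads improved. A patient who rises from 100 to 290 reads as declined. The auscultation and film items treat no change as worsening, so the four items do not share one meaning of improvement.

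At stake is a secondary outcome that directly measures the lung injury the treatment is meant to act on. A moderate effect on the lung would be more likely to be reported as no difference, and a relative risk of improvement cannot show how far oxygenation moved.

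**Working it through.** **The plan's own figure.** Mortality 30% v 15%, alpha 5% (two-sided assumed), power 80%, pooled proportion 0.225:

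n = [1.96·√(2·0.225·0.775) + 0.8416·√(0.30·0.70 + 0.15·0.85)]² / 0.15² = (1.1575 + 0.4889)² / 0.0225 = 120.5, so 121 per group.

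With the continuity correction this becomes 133.5, so 134. The stated 133 is reproduced within rounding. It is taken below as n per group.

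**PaO2/FiO2 cut v full scale.** Assumptions, none from the article: normal values, a shift of d SD between groups, and a control proportion pC at or above 300 of 30%, 50% or 70%.

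- Full scale: power = Φ(d/√(2/n) − 1.96).
- Cut: pT = Φ(Φ⁻¹(pC) + d), then the two-proportion formula at n = 133.

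Example, d = 0.344 and pC = 50%:

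- Full scale: 0.344/√(2/133) = 2.805; Φ(2.805 − 1.96) = 80%.
- Cut: pT = 63.4%. Pooled SE = √(2·0.567·0.433/133) = 0.0608. Unpooled SE = √((0.25 + 0.634·0.366)/133) = 0.0602. Power = Φ((0.134 − 1.96·0.0608)/0.0602) = 60%.
- Loss: 20 points.

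| d (SD) | Full scale | Cut, pC 30% | Cut, pC 50% | Cut, pC 70% | Loss (points) |
|---|---|---|---|---|---|
| 0.2 | 37.1% | 24.0% | 25.3% | 22.6% | 12 to 15 |
| 0.3 | 68.7% | 47.4% | 49.1% | 43.1% | 20 to 26 |
| 0.344 | 80.0% | 58.5% | 60.0% | 52.8% | 20 to 27 |
| 0.4 | 90.4% | 72.0% | 73.0% | 65.0% | 17 to 25 |
| 0.5 | 98.3% | 89.2% | 89.4% | 82.2% | 9 to 16 |

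The loss over this grid is 9 to 27 points. If the entry value correlates 0.5 with the day-5 value, adjustment replaces √(2/n) by √(2·0.75/n). At d = 0.344 power is then Φ(0.344/√(1.5/133) − 1.96) = Φ(1.28) = 90%.

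**Three-of-four v the 0-to-4 count.** Simulation at 133 per group, 3,000 trials per setting: four equally correlated normal parameters (correlation 0.3 or 0.6), an equal shift of 0.2 to 0.4 SD, each item improved in 50% or 65% of controls. Chi-squared on three-of-four is compared with Mann-Whitney on the count.

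| Shift | Correlation | Control item rate | Three of four | Count 0 to 4 | Loss (points) |
|---|---|---|---|---|---|
| 0.25 | 0.3 | 50% | 59.7% | 73.4% | 13.7 |
| 0.35 | 0.6 | 65% | 72.1% | 82.9% | 10.8 |
| 0.40 | 0.3 | 50% | 94.5% | 98.2% | 3.7 |

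These rows include the largest and smallest losses over the grid. Allowing for simulation error, the range is about 3 to 14 points. The smallest losses arise where power is already near its ceiling.

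**The case against.** - **The article does not say that lung evolution is tested only as yes/no.** A reader might infer this. But the article grades improvement as early or late, allows a t-test on means and names no test for this outcome, and a fuller analysis plan may exist. This stands, so the claim is limited to how the outcome is defined and to the natural reading of the analysis. No mean-based lung outcome is defined, however, and the t-test is not tied to any lung measure.
- **Lung evolution is not the only graded efficacy outcome beside mortality.** A reader might think so. Durations of ventilation, ICU stay and hospital stay are also secondary outcomes, and two of them have their own sample-size figures. This stands and lowers the stakes.
- **No single power loss belongs to this trial.** A reader might take the illustrated figures as a property of the design. They depend on assumed effects, correlations and improvement rates. The item and composite losses are also separate quantities and should not be merged into one range. This stands.
- **The value 300 is not arbitrary.** It is the article's own oxygenation threshold within its definition of hypoxemia, so the item asks whether the patient is outside that range. That is a fair reason to report the proportion. It does not make the item a measure of improvement when entry at or above 300 is possible.
- **The simulation simplifies the items.** Auscultation and film are scored as change from an earlier grade, and hematometry can count as improved with transfusion support. This affects the size of the loss. The direction was the same in every shift-type setting tried.

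**Conclusion.** The point holds at modest priority. The article turns graded, repeated lung data into day-5 yes/no items and then into a single three-of-four score. The PaO2/FiO2 item can record improvement without change and decline despite a large rise; that follows from the text and needs no assumed figures.

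The power cost is illustrative: roughly 9 to 27 points for the PaO2/FiO2 cut and about 3 to 14 points for three-of-four against the count. Both rest on 133 per group, two-sided 5%, shift-type effects on normal scales and the assumed rates and correlations shown. The trial was not sized on this outcome, so the mortality sample size and the primary comparison are untouched.

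**What to change.** Add to *Statistical analysis*:

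1. Day-5 PaO2/FiO2 is compared on its full scale, adjusted for the entry value, by rank-based ANCOVA. Patients who die before day 5 take the worst rank.
2. The number of improved parameters (0 to 4, deaths lowest) is compared by Wilcoxon test or a proportional-odds model.
3. State how patients discharged before day 5 enter both analyses (for example with the last recorded value). State also how patients who did not receive their assigned treatment enter, since the article deems them treatment failures and that maps directly only onto a yes/no score.
4. Keep the three-of-four percentage and its relative risk as a summary.

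The cost is a few sentences. No extra patients, visits or measurements are needed, because the values are already collected. The downside is that a rank or mean difference is less immediately readable than a percentage improved, which is why the percentage stays.

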#### Respiratory Infection

Respiratory infection is defined by the presence of a recent pulmonary infiltrate or an increase in pre-existing infiltrate, in association with at least two or three clinical criteria: a) fever (axillary temperature of 37.8°C), b) changes in leukometry (leukocytes <4000 cel/mm3 or >11000 cel/mm3), c) purulent tracheo-bronchial secretion.

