## Methods/Design

### Study design

The study is a double-blind randomized clinical trial - RCT--which evaluates the efficacy of the use of pulse therapy with methylprednisolone compared to a placebo in patients with lung involvement in leptospirosis. The patients are randomly divided into two clearly-defined groups: a) the study group, which receives conventional treatment associated with endovenous pulse therapy with 1 g methylprednisolone for three consecutive days and b) the control group, which receives the conventional treatment plus a placebo. The patients are followed until such a time as they are discharged from hospital or die. The primary endpoint is taken to be mortality from leptospirotic pneumonitis. The secondary end-points are: a) evolution of lung disease; b) the occurrence of nosocomial respiratory infection; c) duration of mechanical ventilation; d) duration of intensive care unit (ICU) stay; e); duration of hospital stay; f) occurrence of other infection-related complications; h) Other respiratory complications; and i) adverse effects of methylprednisolone.

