### Definition of Terms

#### Diagnosis of Leptospirosis

Patients are diagnosed as having leptospirosis when they present epidemiological information relating to contact with flooded areas or professional exposure; clinical criteria include the sudden onset of fever and myalgia; and three of the following laboratory criteria: normal leukometry or leukocytosis, thrombocytopenia, hyperbilirubinemia, increased muscle enzymes and the absence of hyperkalemia. Diagnosis of leptospirosis is confirmed by a serological test (antibody count using the ELISA method) collected after the seventh day and repeated after the tenth day if necessary.

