#### Diagnosis of Leptospirotic pneumonitis

Diagnosis of leptospirotic pneumonitis is based on the presence of pulmonary interstitial infiltrate or bilateral alveolar-interstitial infiltrate on chest x-ray, in association with at least one of the following findings: alterations found by lung auscultation (fine crackles), cough, dyspnea, drop in hemoglobin, hemoptoic sputum, hemoptysis and hypoxemia, the latter being defined as a partial pressure of oxygen (PaO_2_) of less than 60 mmHg in arterial gasometry or peripheral saturation of hemoglobin with oxygen (SpO_2_) of less than 90% on pulse oximetry, both under ambient conditions, or an oxygenation índex (relation between PaO_2_/FiO_2_) of <300 mmHg.

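### The nosocomial respiratory infection outcome has no onset rule, so progression of the leptospirotic pneumonitis can be counted as hospital infection

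*Protocol article*

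**What the plan says.** The Study design section lists "the occurrence of nosocomial respiratory infection" among the secondary end-points. The abstract and Table 1 use the same name.

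The only definition stands under Respiratory Infection, a heading that omits the word nosocomial: "Respiratory infection is defined by the presence of a recent pulmonary infiltrate or an increase in pre-existing infiltrate". The number of clinical signs that must accompany the infiltrate is worded as "in association with at least two or three clinical criteria". The three criteria are fever (axillary temperature of 37.8°C), leukocytes below 4000 or above 11000 per mm3, and purulent tracheo-bronchial secretion. No time since admission or randomisation is given, and nothing separates infection from the disease under study.

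The entry disease is described with overlapping signs:

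- **Infiltrate** (Diagnosis of Leptospirotic pneumonitis): the diagnosis requires "presence of pulmonary interstitial infiltrate or bilateral alveolar-interstitial infiltrate on chest x-ray".
- **Fever** (Diagnosis of Leptospirosis): "clinical criteria include the sudden onset of fever and myalgia".
- **Leukocytes** (same section): three laboratory criteria are needed from "normal leukometry or leukocytosis, thrombocytopenia, hyperbilirubinemia, increased muscle enzymes and the absence of hyperkalemia".

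Under Evolution of lung disease, the day-5 film is scored as improving or worsening: "It is considered to have worsened when the parameters have remained unchanged or seen an increase".

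**The concern.** The outcome is named for an event acquired in hospital, but the rule that counts it contains no hospital-acquired element. Of its three clinical signs, only purulent secretion is absent from the article's criteria for leptospirosis and its pneumonitis. If two signs are enough, fever plus leukocytosis will do, and growth of the entry infiltrate supplies the rest.

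Bacterial infection is listed as a possible adverse effect of methylprednisolone, so this outcome bears on harm. The error also need not be equal between arms. The trial's hypothesis is that the steroid improves the pneumonitis. If it does, fewer progressions are available to be miscounted in the steroid arm, and that shortfall offsets any true excess of infection. Randomisation and blinding do not remove this, because it runs through the intended effect of the drug. The error points towards reassurance.

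**Working it through.** **Step 1. Does the printed rule admit progression?** Each element is compared with what the study disease can supply.

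| Element of the definition | Can the study disease supply it? |
|---|---|
| Recent infiltrate, or increase in a pre-existing one | Yes. All patients have an infiltrate at entry, and its growth is scored as worsening of the pneumonitis |
| Fever | Yes, possible. Part of the clinical diagnosis |
| Leukocytes above 11000 | Possible, not required. A normal count also meets the entry criterion, and no threshold is given there |
| Purulent secretion | Not listed among the signs of the disease |

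If two signs suffice, progression with fever and leukocytosis qualifies. If all three are needed, purulent secretion becomes compulsory and this route closes. The printed threshold allows either reading.

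**Step 2. Inputs for an illustration.** The article gives no expected rate, effect or sample size for this outcome, so there is no figure of its own to reproduce. The only figure used is the 133 per group in the Sample size section, which was calculated for mortality of 30% v 15%. The two-sided formula with continuity correction gives 134, so it reproduces closely. Everything else is assumed:

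- true hospital-acquired respiratory infection, *p*: 20% steroid, 10% placebo;
- share of truly uninfected patients whose progression meets the definition, *q*: varied below.

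**Step 3. Formula.** Counted rate = *p* + (1 − *p*)*q*.

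With no misclassification: 20% v 10%, relative risk 2.0, power of the two-sided 5% chi-squared test about 63% at 133 per group.

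*Steroid has no effect on the pneumonitis (equal q):*

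- *q* = 10% in both arms: 0.20 + 0.80 × 0.10 = 0.28 v 0.10 + 0.90 × 0.10 = 0.19. Relative risk 1.47, power about 41%.
- *q* = 20% in both arms: 0.20 + 0.80 × 0.20 = 0.36 v 0.10 + 0.90 × 0.20 = 0.28. Relative risk 1.29, power about 29%.

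*Steroid halves progression:*

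- *q* = 5% v 10%: 0.20 + 0.80 × 0.05 = 0.24 v 0.10 + 0.90 × 0.10 = 0.19. Relative risk 0.24/0.19 = 1.26, power about 17%.
- *q* = 10% v 20%: 0.20 + 0.80 × 0.10 = 0.28 v 0.10 + 0.90 × 0.20 = 0.28. Relative risk 1.0, so the excess disappears.

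Equal misclassification pulls the relative risk towards 1. Misclassification that the drug reduces pulls it further.

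**The case against.** Several objections have force.

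- **Cases at entry.** A reader might infer that patients with fever and leukocytosis already meet the outcome at randomisation. The document does not support that. The outcome is called nosocomial, the definition contrasts a recent infiltrate with a pre-existing one (in this population the entry infiltrate is naturally the pre-existing one), and the Population section excludes other active bacterial infection. No figures here rest on entry cases.
- **Overlap of signs is possible, not certain.** The diagnosis speaks of sudden onset of fever, not of 37.8°C at randomisation, and a normal leukocyte count satisfies the laboratory criterion. Progression can count as infection; it need not.
- **Other infection outcomes exist.** Sepsis, septic shock, pulmonary abscess, fungemia, empyema, and bacterial and fungal infection appear under the other complications and the adverse effects. The article does not rank this outcome as its main measure of infection harm, so what is blurred is one respiratory component.
- **Sharing a film is no error in itself.** A true hospital pneumonia would also worsen the day-5 film. The fault is that nothing tells the two causes apart.
- **The sizes are assumed.** This is correct. A reader might go further and infer that a doubled risk would appear as protection. That needs heavier differential misclassification: 15% v 30% gives 32% v 37%, relative risk 0.86. Nothing in the document supports such shares.
- **A condensed article may leave the onset window to the full protocol.** This would answer a bare omission. Here a definition with numerical thresholds is printed, and as printed it admits progression. The word nosocomial does not cure this, because the pneumonitis can also progress after admission.

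**Conclusion.** The point holds for progression after entry. As printed, the definition can count worsening leptospirotic pneumonitis as nosocomial respiratory infection, and its threshold for clinical signs is unclear. The direction follows from the design: dilution if the steroid leaves the pneumonitis unchanged, and further loss of a true excess if the steroid slows it.

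The size cannot be derived from the document. The relative risks of 1.26 and 1.0, against a true 2.0, rest on assumed infection rates, assumed progression shares, a halving of progression by the drug, and progression acting independently of infection. They also take two signs as sufficient.

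The matter concerns one secondary outcome among several that touch on infection. It deserves correction because the outcome bears on harm, the error can reassure falsely, and the repair is small. The mortality comparison is not affected.

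**What to change.** Amend the definition under Respiratory Infection as follows:

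1. Count only episodes with onset after randomisation and at least 48 hours after hospital admission, with the infiltrate new or increased relative to the entry film.
2. State the threshold as at least two of the three signs.
3. Report alongside, as a sensitivity analysis, a stricter definition that requires purulent secretion plus one of the other two signs.

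Items 1 and 2 make the rule match the outcome's name and remove early progression, but progression after the 48-hour point can still qualify. Item 3 is what separates that from infection, so the two results should be read together.

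Do not restrict the outcome to lung zones uninvolved at entry. Patients graded as whole-lung in Table 3 have no such zone, and their infections would be missed.

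The cost is one onset date on the case report form and one extra analysis. The entry film already exists for every patient, because the diagnosis depends on it. The stricter version will miss some true infections in both arms, which is why it accompanies the main definition and does not replace it. Only outcome classification changes, not patient care.

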**Study design:**

This is a randomized double-blind clinical trial to test the efficacy of pulse treatment with methylprednisolone in patients with leptospirotic pneumonitis, compared with a placebo. The patients are recruited from three hospitals in the city of Recife, in the Brazilian State of Pernambuco. The exclusion criteria include patients aged under 15 years, a history of hypersensitivity to the use of corticosteroids, the presence of active infection of fungal, tuberculous or bacterial origin apart from the infection by leptospira itself, the presence of hemoconcentration or atypical lymphocyte count on admission to hospital, the presence of co-morbidities that could be responsible for the radiological and gasometric alterations used to diagnose leptospirotic pneumonitis, evidence of recent cranial trauma, neurosurgery, peptic ulcer, and participation in another clinical trial. The patients are followed until they are discharged from hospital or die. The intervention consists of endovenous pulse treatment with 1 g methylprednisolone for three consecutive days in the study group and a placebo in the control group. The primary end-point is mortality from leptospirotic pneumonitis. The secondary end-points are: evolution of lung disease; the occurrence of nosocomial respiratory infection; duration of mechanical ventilation; duration of intensive care unit (ICU) stay; duration of hospital stay; occurrence of other infection-related complications; other respiratory complications; and adverse effects of methylprednisolone. The study is designed to recruit 266 patients and has a statistical "power" of 80% to detect a 50% reduction in mortality.

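### The nosocomial respiratory infection outcome has an ambiguous threshold and no onset time, so it does not reliably separate infection from progression of the pneumonitis

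*Protocol article*

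**What the plan says.** The Abstract and the Study design section of the protocol article both list "the occurrence of nosocomial respiratory infection" among the secondary end-points. Table 1 also names it as nosocomial. The section that defines it is headed only Respiratory Infection and gives an operative rule in two parts:

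- a radiological element: "presence of a recent pulmonary infiltrate or an increase in pre-existing infiltrate";
- a clinical element, "in association with at least two or three clinical criteria", from a list of three: "fever (axillary temperature of 37.8°C"), a changed white count ("leukocytes <4000 cel/mm3 or >11000 cel/mm3"), and "purulent tracheo-bronchial secretion".

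The rule sets no minimum time from admission or randomisation. It does not require fever or white-count change to be new.

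Three other sections bear on this:

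- Diagnosis of Leptospirosis: "clinical criteria include the sudden onset of fever and myalgia", and the laboratory list, of which three items are needed, begins "normal leukometry or leukocytosis, thrombocytopenia, hyperbilirubinemia".
- Diagnosis of Leptospirotic pneumonitis: a chest x-ray infiltrate is required, so every participant has one at entry.
- Evolution of lung disease: a greater radiological extent on day five is scored as worsening of the pneumonitis.

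**The concern.** An outcome called nosocomial infection should capture infection acquired in hospital. Here two elements of the definition are loose.

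First, the number of clinical criteria can be read in two ways, and the choice decides whether the one criterion outside the picture of the index disease has to be present. Secondly, nothing in the operative rule gives effect to the word nosocomial.

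The stake is the reading of a safety-relevant comparison. The article lists bacterial and fungal infection among the possible adverse effects of methylprednisolone, and the trial also tests whether the drug improves the lung disease. If one radiographic change can count both as failed lung evolution and as infection, the infection comparison mixes a possible harm with a possible benefit. Two assessors could also classify the same patient differently, depending on how they read the threshold.

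**Working it through.** **Plan's own figure.** The article gives no rate or sample size for respiratory infection, so there is none to reproduce. The mortality sample size (30% v 15%, 5% significance, 80% power) comes to 134 per arm with a two-sided, continuity-corrected formula, against the stated 133. It is used below only as the arm size.

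**Step 1: compare the definitions.**

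| Element of respiratory infection | Can the index disease supply it, by the article's own definitions? |
|---|---|
| Increase in existing infiltrate | Yes: an infiltrate is required at entry, and an increase is scored as worsening pneumonitis |
| Fever | Yes: part of the clinical criteria for leptospirosis |
| Leukocytes above 11,000 | Yes: leukocytosis is an accepted laboratory finding, though not a required one |
| Leukocytes below 4,000 | Not in the listed picture |
| Purulent secretion | Not in the listed picture |

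**Step 2: apply each reading of the threshold.**

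- *Two suffice.* Infiltrate increase, fever and leukocytosis meet the rule. All three can come from leptospirotic pneumonitis, and neither of the last two rows is needed.
- *All three needed.* Purulent secretion becomes mandatory and the overlap largely disappears.

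The ambiguity therefore changes what is measured.

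**Step 3: timing.** The outcome's name implies hospital acquisition, but the rule has no time element. Read alone, it does not exclude worsening soon after admission.

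**Step 4: what misclassification could do (illustration; every rate is an assumption).** Let *t* be the true infection rate and *f* the proportion of uninfected patients whose progression meets the rule. Then observed rate = *t* + (1 − *t*) × *f*. Take *t* = 10% on placebo and 20% on methylprednisolone, a true relative risk (RR) of 2.0.

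| *f* placebo / steroid | Observed placebo | Observed steroid | RR |
|---|---|---|---|
| 0 / 0 | 10% | 20% | 2.00 |
| 10% / 10% | 0.10 + 0.90 × 0.10 = 19% | 0.20 + 0.80 × 0.10 = 28% | 1.47 |
| 20% / 20% | 28% | 36% | 1.29 |
| 30% / 30% | 37% | 44% | 1.19 |
| 10% / 5% | 19% | 0.20 + 0.80 × 0.05 = 24% | 1.26 |
| 20% / 10% | 28% | 0.20 + 0.80 × 0.10 = 28% | 1.00 |

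Power = Φ[(difference − 1.96 × SE₀) / SE₁], with SE₀ = √(2p̄(1 − p̄)/n), SE₁ = √([p₁(1 − p₁) + p₂(1 − p₂)]/n) and n = 133. For 10% v 20%: SE₀ = 0.0438, SE₁ = 0.0434, (0.10 − 0.0858)/0.0434 = 0.33, power 63%. With equal misclassification of 10%, 20% or 30%, power is 41%, 29% or 21%.

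Equal misclassification dilutes the contrast. If the drug also slows progression, as in the last two rows, the contrast shrinks further and can vanish.

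**The case against.** Much of the case on the other side stands.

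- *The overlap depends on the reading.* It applies only if two criteria suffice. A reader might infer that the definition is always met by worsening pneumonitis, or that it can never separate the two. The text does not support that: it can be met in this way, on one reading.
- *Entry criteria are weaker than they look.* A normal white count satisfies the same laboratory item as leukocytosis, and only three of the five items are needed. The fever criterion describes how the illness began, not the temperature after randomisation. How many patients carry both signs forward is unknown.
- *The name and the exclusions help.* Nosocomial implies hospital acquisition, and active bacterial infection other than leptospira is excluded at entry. So one cannot say that every day-one worsening would be counted. But the article gives a full operative rule with numerical cut-offs, and that rule does not carry the name into a time limit. The entry exclusion also does not separate later progression from superinfection.
- *Infection is recorded elsewhere.* Sepsis, septic shock, fungemia, pulmonary abscess, empyema, and bacterial and fungal infection as adverse effects all have their own place. This is one of several secondary end-points, and nothing in the article ranks it above the others.
- *The trial is double-blind.* Blinding evens out ascertainment. It does not stop a real effect on pneumonitis from changing the number of false positives by arm.

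A reader might go further and infer that a true harm would appear as a benefit. Harsher assumed rates do give that: *f* of 30% v 15% in the formula above returns an RR of 0.86. It follows only from the rates chosen, none of which is in the article, and is not evidence here. Nor does the article say that the drug itself alters fever or white count, so the point does not rest on that.

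**Conclusion.** The concern holds in a limited form. The definition contains two different thresholds and no onset time. On the two-criteria reading it can be met by progression of leptospirotic pneumonitis alone, so this secondary outcome does not reliably separate infection from disease. If methylprednisolone slows progression, a rise in infection may be diluted or masked.

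The threshold ambiguity and the overlap follow from the text. The size of the effect does not: the rates in the illustration are assumed and show only the direction and possible range of the distortion. The primary outcome, mortality, is unaffected. The definition should be corrected because the change is small and the result would otherwise be hard to interpret in either direction.

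**What to change.** Reword the Respiratory Infection definition as follows:

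1. State one threshold: the infiltrate element plus at least two of the three clinical criteria.
2. Count an event only if it starts at least 48 hours after admission and also after randomisation. The 48 hours is this review's proposal, not a figure from the article.
3. Report infiltrate progression before that point only under Evolution of lung disease.
4. Add a sensitivity analysis in which purulent secretion must be one of the criteria met. This is needed because progression after 48 hours with fever and leukocytosis would still satisfy rule 1. It is better as a sensitivity analysis than as the main definition, since requiring it throughout could miss true infections.

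The cost is wording and one further analysis. All the items are already named in the article, and lung disease is already assessed radiologically every day to day seven and again on days 14 and 28. The downside is slightly fewer events and some early true infections left uncounted.
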